### **10.3 Other study parameters**

Continuous data with normal distribution will be presented as mean  $\pm$  SD. Variables with a skewed distribution will be presented as median and range. Categorical variables will be expressed as frequencies and percentages. Confidence intervals (CIs) are expressed to a level of 95%.

To test for normal distribution of data, the data will be visually inspected, a Q-Q plot will be constructed and in case of doubt a test for normality will be used (e.g. Shapiro-Wilk test/Kolmogorov-Smirnov test).

For comparing normally distributed continuous data, we will use the Student's t-test. In variables with non-homogeneity of variance, the Welch test will be used.

For comparing non-normally distributed continuous data, the Mann-Whitney U test will be used.

For comparing categorical data the chi-square test will be used and the Fisher's exact test will be used in variables containing low numbers.

All P-values are two-sided and a P-value  $< 0,05$  is considered statistically significant. Statistical analysis will be performed using SPSS 22 (SPSS Inc, Chicago, IL, USA).

### **10.4 Interim analysis**

Not applicable.

## **11. ETHICAL CONSIDERATIONS**

### **11.1 Regulation statement**

This study will be conducted according to the principles of the Declaration of Helsinki (Seventh revision, Fortaleza 2013), in accordance with the Medical Research Involving Human Subjects Act (WMO), and also in accordance with the International Conference on Harmonisation Good Clinical Practice Guidelines.

### **11.2 Recruitment and consent**

It is the responsibility of the investigator, or a person designated by the investigator, to obtain written informed consent from each individual participating in this study after adequate explanation of the aims, methods, objectives and potential hazards of the study. It will also be explained to patients that they are completely free to refuse to enter the study or to withdraw from it at any time for any reason. Patients will be given a period of one week to consider participation before they are asked to sign the informed consent form.

If new safety information results in significant changes in the risk/benefit assessment, the consent form will be reviewed and updated if necessary. All patients (including those already being treated) will be informed of the new information, given a copy of the revised form and asked to give their consent to continue in the study.

The patient information letter and informed consent form are attached as separate documents.

### **11.3 Objection by minors or incapacitated subjects**

Not applicable.

### **11.4 Benefits and risks assessment, group relatedness**

In this trial both groups are treated with a drug, known to be beneficial to hand eczema in a considerable amount of patients. So the intended benefit of both study drugs is to reduce the severity of hand eczema.

We hypothesize that azathioprine has a superior efficacy compared to alitretinoin (the registered treatment for hand eczema in The Netherlands) in severe chronic non-hyperkeratotic hand eczema. If this hypothesis is confirmed, there could be a practical, as well as a financial implication. Practically, more responding patients to azathioprine leads to a greater beneficial effect on hand eczema in this patient group. Financially, azathioprine is a lot less expensive than alitretinoin. If azathioprine shows superior efficacy in non-hyperkeratotic hand eczema, this could lead to an official registration. This,

in turn, could mean a decrease in financial burden for the treatment of all non-hyperkeratotic hand eczema patients in the population.

A risk assessment is carried out in chapter 13.

### **11.5 Compensation for injury**

The sponsor/investigator has a liability insurance which is in accordance with article 7, subsection 6 of the WMO.

The sponsor (also) has an insurance which is in accordance with the legal requirements in the Netherlands (Article 7 WMO and the Measure regarding Compulsory Insurance for Clinical Research in Humans of 23th June 2003). This insurance provides cover for damage to research subjects through injury or death caused by the study.

1. € 450.000,-- (i.e. four hundred and fifty thousand Euro) for death or injury for each subject who participates in the Research;
2. € 3.500.000,-- (i.e. three million five hundred thousand Euro) for death or injury for all subjects who participate in the Research;
3. € 5.000.000,-- (i.e. five million Euro) for the total damage incurred by the organisation for all damage disclosed by scientific research for the Sponsor as 'verrichter' in the meaning of said Act in each year of insurance coverage.

The insurance applies to the damage that becomes apparent during the study or within 4 years after the end of the study.

### **11.6 Incentives**

Not applicable.

## **12. ADMINISTRATIVE ASPECTS, MONITORING AND PUBLICATION**

### **12.1 Handling and storage of data and documents**

Data will be handled confidentially. Data derived from the questionnaires and other paper source documents will be coded using sequential administration numbers. A subject identification code list is used to link the data to the subjects. The code is not based on the patient initials and birth-date. The code will be safeguarded by the principal investigator, [name]. The documents will be stored in a locked room. The digital source data will be saved in subsections of the subjects medical file. These data will be accessible to the principal investigator and the investigator, and also to the treating physician if this is not the investigator. Data will not be accessed by the blinded efficacy assessors.

All data will be recorded in electronic Case Report Forms in Utopia, software for Electronic Data Capture (, developed by the Trial Coordination Center, linked to the University Medical Center Groningen. The eCRFs will only be accessible with the username and password of the responsible investigator.

Data will be saved for 15 years after completion of this study.

All the data will be saved in accordance with the Dutch Personal Data Protection Act.

### **12.2 Monitoring and Quality Assurance**

A monitor of the University Medical Center Groningen will carry out monitoring of this study. The monitor will get read-only access to the digital and paper documents of participants. Goal of this monitoring is to review if:

- the rights and wellbeing of subjects are being protected
- the reported data is right and fully reproducible
- the execution of the study is in accordance with this protocol and relevant legal requirements.

### **12.3 Amendments**

A 'substantial amendment' is defined as an amendment to the terms of the METC application, or to the protocol or any other supporting documentation, that is likely to affect to a significant degree:

- the safety or physical or mental integrity of the subjects of the trial;
- the scientific value of the trial;
- the conduct or management of the trial; or
- the quality or safety of any intervention used in the trial.

All substantial amendments will be notified to the METC and to the competent authority.

Non-substantial amendments will not be notified to the accredited METC and the competent authority, but will be recorded and filed by the investigator.

#### **12.4 Annual progress report**

The investigator will submit a summary of the progress of the trial to the accredited METC once a year. Information will be provided on the date of inclusion of the first subject, numbers of subjects included and numbers of subjects that have completed the trial, serious adverse events/ serious adverse reactions, other problems, and amendments.

#### **12.5 End of study report**

The investigator will notify the accredited METC and the competent authority of the end of the study within a period of 90 days. The end of the study is defined as the last patient's last visit.

In case the study is ended prematurely, the investigator will notify the accredited METC and the competent authority within 15 days, including the reasons for the premature termination.

Within one year after the end of the study, the investigator will submit a final study report with the results of the study, including any publications/abstracts of the study, to the accredited METC and the Competent Authority.

#### **12.6 Public disclosure and publication policy**

This study is designed honoring the CCMO statement on publication policy.

This is an investigator initiated study. The results of the study will be made public unreservedly; they will be offered for publication in a peer reviewed journal. In a publication all data will be handled anonymously.

The study will be registered in a public trial register before the inclusion of the first patient.

### 13. STRUCTURED RISK ANALYSIS

#### 13.1 Potential issues of concern

Both alitretinoin and azathioprine are drugs that are routinely used in medicine and particularly in the treatment of hand eczema in our department. The information asked in this chapter is described in detail in the SPC text documents of the study drugs. (10,18) These texts are used as important sources on which this protocol is based.

##### a. Level of knowledge about mechanism of action

For this section the reader is referred to paragraph 6.1 and the SPC text of alitretinoin and azathioprine. (10,18)

##### b. Previous exposure of human beings with the test product(s) and/or products with a similar biological mechanism

For this section the reader is referred to paragraph 6.3 and the SPC text of alitretinoin and azathioprine. (10,18)

##### c. Can the primary or secondary mechanism be induced in animals and/or in *ex-vivo* human cell material?

For this section the reader is referred to paragraph 6.2 and the SPC text of alitretinoin and azathioprine. (10,18)

##### d. Selectivity of the mechanism to target tissue in animals and/or human beings

For this section the reader is referred to paragraph 6.1 and the SPC text of alitretinoin and azathioprine. (10,18)

##### e. Analysis of potential effect

*Alitretinoin (from SPC text) (10)*

The recommended dose range for alitretinoin is 10 mg - 30 mg once daily.

The recommended start dose for alitretinoin is 30 mg once daily. A dose reduction to 10 mg once daily may be considered in patients with unacceptable adverse reactions to the higher dose. In studies investigating 10 mg and 30 mg daily doses, both doses resulted in clearing of the disease. The 30 mg dose provided a more rapid response and a higher response rate. The 10 mg daily dose was associated with fewer adverse events.

A treatment course of alitretinoin may be given for 12 to 24 weeks depending on response. Discontinuation of therapy should be considered for patients who still have severe disease after the initial 12 weeks of treatment. In the event of relapse, patients may benefit from further treatment courses of alitretinoin.

The capsules should be taken with a meal once daily.

Alitretinoin should not be prescribed if the patient's eczema can be adequately controlled by standard measures, including skin protection, avoidance of allergens and irritants, and treatment with potent topical corticosteroids.

Risks of alitretinoin treatment are described in paragraph 6.4.

#### *Azathioprine (from SPC text) (18)*

In general, the starting dosage is 1-3mg/kg/body weight/day and should be adjusted according to the clinical response (which may not be evident for weeks or months) and haematological tolerance.

The maintenance dosage required may range from less than 1mg/kg body weight/day to 3mg/kg/body weight/day depending on the clinical condition being treated and the individual patient response including haematological tolerance.

Risks of azathioprine treatment are described in paragraph 6.4 and 6.5 (regarding TPMT measurement).

#### f. Pharmacokinetic considerations

##### *Alitretinoin (from SPC text) (10)*

###### Absorption

The absorption of alitretinoin from the gastro-intestinal tract is variable and dose-proportional over the therapeutic range from 10-30 mg. The absolute bioavailability of alitretinoin has not been determined. When alitretinoin is taken with food, the systemic exposure is enhanced by a factor of 4 and the variability of exposure is decreased. Therefore, alitretinoin should be taken with a meal.

###### Distribution

Alitretinoin strongly binds to plasma proteins. The volume of distribution of alitretinoin in man has not been determined, but animal studies indicate a volume of distribution greater than the extracellular volume.

###### Metabolism

Alitretinoin is metabolized by oxidation in the liver by CYP3A4 isoenzymes into 4-oxo-alitretinoin. Both compounds undergo isomerization into all-trans retinoic acid and 4-oxo-all-trans retinoic acid. After oral administration, the contribution of the metabolites in plasma to the systemic exposure of alitretinoin is approximately 35% to 80% for 4-oxo-alitretinoin. The major metabolite 4-oxo-alitretinoin is further glucuronidated and eliminated in urine. Alitretinoin is degraded similarly to vitamin A by sequential cleavage of

the carbon-side chain. During a 12-to 24-week treatment period with 10 or 30 mg dose, the exposure to alitretinoin remained stable.

#### Elimination

Alitretinoin is an endogenous retinoid. Alitretinoin concentrations return to normal range within 1 to 3 days treatment cessation. Excretion of radio-labelled alitretinoin was complete with approximately 94% of the dose recovered. Radio-labelled material was eliminated mainly in urine and a smaller fraction (approx. 30%) in faeces. The most abundant excretion compound is the glucuronide of 4-oxo-alitretinoin amounting to 6.5% of the dose in urine. Elimination half-life of unchanged alitretinoin ranges between 2 to 10 hours. Alitretinoin and its 4-oxo-metabolite do not accumulate.

#### Pharmacokinetic in special populations

In a pharmacokinetic study in patients, gender, weight and age did not affect the pharmacokinetics of alitretinoin. The pharmacokinetics of alitretinoin in CHE patients was similar to that in healthy volunteers. Alitretinoin kinetics has not been studied in patients with hepatic or with severe renal insufficiency or in patients below 18 years.

#### *Azathioprine (from SPC text) (18)*

Azathioprine is well absorbed following oral administration. Peak plasma concentrations are reached 1-2 hours after taking a dose. Azathioprine is distributed rapidly throughout the body. The plasma half life is 3-5 hours. Only 30% of the medicinal product binds to plasma proteins. 12.5% enter the cerebrospinal fluid.

Azathioprine is extensively metabolised to 6-thioinosinic acid and methyl mercaptopurine-ribonucleotide, which, in part, are responsible for the effect of the medicinal product. The effect in-vivo is complicated by the action of methyl-nitroimidazole, which is also found.

Up to 50% of a dose is excreted in urine during the first 24 hours after administration, with approximately 10% as unchanged substance. Only 12.6% of the dose is excreted during 48 hours with the faeces. There is no evidence for enterohepatic circulation.

A lowered dosage for patients with reduced renal function may be necessary, probably as a result of reduced elimination of the active metabolites of azathioprine.

Also in patients with hepatic impairment the metabolism of azathioprine is altered.

Conversion into the active form is reduced, and especially the breakdown to eliminable metabolites is diminished.

Mercaptopurine, a metabolite of azathioprine, has been identified in the colostrum and breast-milk of women receiving azathioprine treatment.

g. Study population

In general, otherwise healthy subject with severe, chronic non-hyperkeratotic hand eczema will be included. Woman with child bearing potential will only be included in the study if they agree to use proper contraceptive methods during study period and up to two months following end of study.

h. Interaction with other products

For this section the reader is referred to paragraph 5.2 and the SPC text of alitretinoin and azathioprine. (10,18)

i. Predictability of effect

No biomarkers for effect have been determined.

j. Can effects be managed?

*Alitretinoin (from SPC text) (10)*

Alitretinoin is a derivative of vitamin A. Alitretinoin has been administered in oncological clinical studies at dosages of more than 10-times of the therapeutic dosage given for chronic hand eczema. The adverse effects observed were consistent with retinoid toxicity, and included severe headache, diarrhoea, facial flushing, hypertriglyceridemia. These effects were reversible.

It can be concluded that the (reversible) effects can be properly managed.

*Azathioprine (from SPC text) (18)*

Symptoms:

In the event of overdose the most likely effect is bone marrow suppression, reaching its maximum mostly 9-19 days after dosing. The principal signs of bone marrow suppression are ulceration of the throat, fever and infections. Furthermore, bruising, bleeding and fatigue may occur. A single large dose of azathioprine is less likely to have a toxic effect than a chronic minor overdosage (e.g. on prescription). Although improvement may be delayed, it usually occurs from the twelfth day after overdose, provided that the patient has not taken a high dose in the meantime.

Treatment:

There is no specific antidote for azathioprine. In the event of overdose, blood count and hepatic function in particular should be monitored. Azathioprine is known to be dialysable and in severe cases dialysis may be used.

It can be concluded that management of severe effects, if needed, could be radical but possible.

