## 4. STUDY POPULATION

### 4.1 Population (base)

The study population will exist of adult patients with severe chronic non-hyperkeratotic hand eczema, visiting the Department of Dermatology of the University Medical Center Groningen.

Non-hyperkeratotic hand eczema will be diagnosed following the criteria of the Danish Contact Dermatitis Group. (6) The severity of the hand eczema at the screening will be graded by means of a Physician Global Assessment using a validated Photoguide. (16)

Woman in the fertile age will be required to use proper contraception methods. Men and women of all ethnicities of 18 years and older will be recruited.

Patients meeting all inclusion criteria, while not meeting any of the exclusion criteria, will be asked to participate.

Our sample size calculation showed a total of 116 patients need to be included. Given the fact that 300-350 individual patients with hand eczema visit our outpatient eczema clinic every year, and the mean severity is high because our department is a tertiary referral center, we believe this number to be feasible.

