##### *General criteria prior to randomization*

- Treatment with alitretinoin or azathioprine in the previous 3 months
- Hyperkeratotic palmar eczema as defined by the Danish Contact Dermatitis Group (6)
- Patients with predominantly atopic dermatitis, in which the hands are also involved. Patients with mild atopic dermatitis, in which the hands are mainly affected are eligible for inclusion.
- Psoriasis
- Active bacterial, fungal, or viral infection of the hands
- Pregnant/lactating or planning to become pregnant during the study period
- Treatment with systemic medication or UV radiation within the previous 4 weeks
- Mentally incompetent
- Immunocompromised status
- Known or suspected allergy to ingredients in the study medications
- Inclusion in a study of an investigational drug within 60 days prior to start of treatment
- Current malignancy (other than successfully treated non-metastatic cutaneous squamous cell or basal cell carcinoma and/or localized carcinoma in situ of the cervix)
- Current active pancreatitis
- Living vaccine (including bacillus Calmette-Guérin (BCG), varicella, measles, mumps, rubella, yellow fever, oral polio and oral typhoid) in the last 2 weeks or the planned application of such a vaccine during the study period
- Evidence of alcohol abuse or drug addiction
- Chronic or recurrent infectious diseases
- Contact sensitizations with clinical relevance to the hands, in which exposure to allergens is not avoided
- Hypervitaminosis A due to the use of vitamin A supplements containing >2000 IU

- Use of drugs with potential to change the effective dose of study drugs within the previous 2 weeks (see paragraph 5.2)

*Laboratory exclusion criteria post randomization*

- Alanine aminotransferase (ALAT) and/or aspartate aminotransferase (ASAT) values > 200% of the upper limit of normal
- Impaired renal function as indicated by a clinically relevant abnormal creatinine value (to be determined by investigator or treating physician)
- Anemia as indicated by a clinically relevant lowered hemoglobin value (to be determined by investigator or treating physician)

*Alitretinoin specific*

- Triglycerides > 200% of the upper limit of normal,
- Cholesterol or low density lipoprotein (LDL) cholesterol values > 200% of the upper limit of normal
- Uncontrolled hypothyroidism (to be determined by investigator or treating physician)

*Azathioprine specific*

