## 8.2 Randomisation, blinding and treatment allocation

Randomization is carried out by a computer program.

This is a study with blinded efficacy assessors, which are unaware of treatment allocation. The participants and treating physician will be aware of treatment allocation. Efficacy assessment will be carried out by physicians or specialized eczema nurses who are experienced in assessing hand eczema by PGA and HECSI in daily practice. Blinding will only be broken after analyzing the data.

At screening visit (-1 week for *alitretinoin*, -5 weeks for *azathioprine*), clinical eligibility of patients is assessed. If eligible, patients are given a least 1 week time to consider participation in the study. If patients choose to participate they will be randomized to alitretinoin or azathioprine treatment (at week 0 for *alitretinoin*, -4 weeks for *azathioprine*). Based on the assigned group, appropriate laboratory assessments will be performed. If these assessments do not show abnormalities as described in the *laboratory exclusion criteria post randomization*, patients will receive the treatment.

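### Known hepatic impairment is not an exclusion in section 4.3, although section 13.1f flags it for both study drugs (minor patient-safety point)

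*Protocol*

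**What the plan says.** **Pharmacokinetics (Protocol 13.1f).** On azathioprine: "Also in patients with hepatic impairment the metabolism of azathioprine is altered". The next sentence gives two changes: "Conversion into the active form is reduced, and especially the breakdown to eliminable metabolites is diminished". On alitretinoin: "Alitretinoin kinetics has not been studied in patients with hepatic or with severe renal insufficiency". The same section describes alitretinoin as oxidised in the liver.

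**Risks (Protocol 6.4).** Liver toxicity is listed among the main risks of azathioprine, and raised transaminases among those of alitretinoin.

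**Eligibility (Protocol 4.3).** The general list, applied before randomisation, does not mention the liver. The laboratory list, applied after randomisation, has one liver item: "Alanine aminotransferase (ALAT) and/or aspartate aminotransferase (ASAT) values > 200% of the upper limit of normal". Its renal item is framed more broadly: "Impaired renal function as indicated by a clinically relevant abnormal creatinine value (to be determined by investigator or treating physician").

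**Enrolment and treatment (Protocol 4.1 and 8.2).** Section 4.1 says: "Patients meeting all inclusion criteria, while not meeting any of the exclusion criteria, will be asked to participate". Section 8.2 says that at the screening visit "clinical eligibility of patients is assessed". Randomisation follows, then the laboratory tests for the assigned arm. The treatment rule begins "If these assessments do not show abnormalities as described in the" post-randomisation laboratory list of 4.3; if that condition is met, treatment is given.

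**The concern.** The protocol identifies a condition in which it knows the handling of one drug changes and has no kinetic data for the other. It does not carry that condition into the eligibility criteria. The transaminase limit is a single laboratory cut-off and does not cover hepatic impairment as such. A diagnosis already in the patient's history therefore leads to exclusion only if ALAT or ASAT also exceeds the limit.

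At stake is the exposure of such a patient to azathioprine for up to 24 weeks at a starting dose set by TPMT activity alone, or to alitretinoin at a fixed 30 mg (section 6.5). Neither starting dose takes liver function into account. Section 13.2 rests its judgement of acceptable risk partly on how strict the entry criteria are, so a condition flagged in 13.1f would be expected among them.

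**Working it through.** No arithmetic decides this point, and no figure in the protocol bears on it. The check sets the sections side by side and follows one patient through them.

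**Step 1: what is flagged and how section 4.3 treats it**

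| | Liver | Kidney |
|---|---|---|
| Azathioprine, 13.1f | Metabolism altered, in two respects | A lower dose may be needed |
| Alitretinoin, 13.1f | Kinetics not studied | Kinetics not studied in severe insufficiency |
| Criterion before randomisation, 4.3 | None | None |
| Criterion after randomisation, 4.3 | ALAT or ASAT > 200% ULN | Clinically relevant abnormal creatinine, judged by a physician |

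Timing is the same for both organs. The difference is in scope: the renal criterion leaves room for clinical judgement, and the liver criterion is a fixed cut-off (200% of ULN = 2 x ULN).

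**Step 2: which general criteria could catch liver disease indirectly**

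Alcohol abuse, chronic or recurrent infection (which would take in chronic viral hepatitis) and current malignancy are excluded before randomisation. Together they remove some causes of liver disease. Impairment from another cause meets none of them.

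**Step 3: one patient followed through the protocol**

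Take a patient with hepatic impairment recorded in the history, ALAT and ASAT at or below 2 x ULN, none of the causes in Step 2, and no other exclusion.

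1. Section 4.1: all inclusion criteria are met and no exclusion applies, so the patient is invited.
2. Section 8.2, screening: clinical eligibility is checked against criteria that do not mention the liver, and the patient passes.
3. Section 8.2, randomisation: the patient is allocated to an arm.
4. Section 4.3, laboratory list: transaminases are within the limit, so no liver exclusion is triggered. Section 8.3 also measures ALP and gamma-GT in both arms, and bilirubin in the azathioprine arm, but 4.3 attaches no exclusion to any of these.
5. Section 8.2, treatment rule: no listed abnormality is present, so the text has treatment follow.

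The patient is eligible on entry and passes the laboratory gate before dosing. Stopping this patient depends on provisions outside the eligibility criteria, which are weighed below.

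**The case against.** **The strongest case against.** Section 13.1f is pharmacokinetic background taken from the product texts, and the protocol contradicts nothing by leaving the condition out of 4.3. Several safeguards stand between such a patient and harm:

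- Section 8.3 provides for a detailed history of newly referred patients and a laboratory analysis to verify contra-indications for systemic treatment.
- Section 6 says the drugs are used as in ordinary practice.
- Section 8.4 lets the investigator withdraw a subject for medical reasons, and the schedules in 8.3 provide for a withdrawal assessment already at baseline.
- Section 6.6 allows dose reduction for abnormal findings.
- Section 8.4.1 requires withdrawal at ALAT or ASAT above 300% of ULN.
- Sections 13.1g and 13.2 describe an otherwise healthy population.

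**What stands.** These safeguards are real and they keep the point minor. They do not remove it. None names hepatic impairment, and 8.2 ties treatment to the listed laboratory abnormalities. Monitoring and dose reduction act after exposure. The description of the population is general (both places say so) and is not a criterion. Section 4.3 already writes down comparable clinical judgements for creatinine, haemoglobin and thyroid function, so leaving this one to ordinary practice is not the protocol's own pattern.

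**Stronger readings that the documents do not support**

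- *Either drug is contraindicated in hepatic impairment.* The protocol does not say so.
- *Azathioprine accumulates and is more toxic in these patients.* Section 13.1f reports less activation as well as less breakdown, and gives no net direction of risk.
- *Discretionary withdrawal is the only thing that could stop such a patient before dosing.* The check for contra-indications in 8.3 is another route.
- *The kidney is screened before randomisation and the liver is not.* Both laboratory criteria come after randomisation.
- *Section 13.2 relies on the entry criteria alone.* It also relies on regular laboratory assessment and on prior experience with both drugs.

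**Conclusion.** The concern holds as a minor patient-safety point about eligibility. The protocol flags hepatic impairment for both drugs, has no exclusion for it when it is known, and as written admits such a patient whenever transaminases are at or below 2 x ULN.

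It rests on one assumption that the documents do not state: that clinically relevant hepatic impairment can be present with ALAT and ASAT within that limit. The documents give no prevalence for this population, so the number affected cannot be estimated and none is offered here. Given the indirect exclusions and the tertiary setting, it may well be very small.

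A reader might infer damage to the sample size or to the primary comparison. The documents do not support that. The chi-square comparison of responders does not depend on this criterion, and section 4.4 already allows for some losses between randomisation and first dose.

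**What to change.** Add one item to the general criteria applied before randomisation in section 4.3, for both arms: *known clinically relevant hepatic impairment, as judged by the investigator or treating physician*. This follows the style already used for creatinine and haemoglobin. It belongs in the pre-randomisation list because a known diagnosis can be read from the history at the existing screening visit, whereas the creatinine criterion has to wait for a test. The transaminase criterion stays as it is.

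The cost is one line of text. No new test, threshold or visit is needed. The downside is very few additional exclusions, all before randomisation.
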